### **EEG measurements**

EEG is continuously recorded using a 40-channel recording system (Refa-40, TMSi B.V., the Netherlands). Electrodes are placed according to the international 10-20 system with a total of 21 leads (MFi B.V.), but replacing electrodes placed at the earlobes (i.e., A1 and A2) with electrodes placed at the mastoids (i.e., M1 and M2). The IES and LEP tasks will use 32 leads EEG. The scalp electrode impedance are kept below 5kΩ. The ground electrode is placed at AFz. Additionally, to detect ocular artefacts, vertical and horizontal EOG are recorded. Two Ag/AgCl electrodes are placed at the outer canthi of both eyes, and two Ag/AgCl electrodes are placed approximately 2 cm above and below the right eye. All signals are sampled at a sampling rate of 1024 Hz and are filtered prior to storage using a first order recursive high-pass filter with a cut-off frequency at 0.1 Hz. Digital markers are recorded by the amplifier indicating the onset of each stimulus.

### **Resting EEG ask description**

Resting-state EEG recordings with open and closed eyes for 5 min in each eye state will be performed [38]. Each recording employs alternating periods with eyes open and closed with a duration of 64-seconds for each period. Subjects face a featureless wall and are instructed not to stare, not to move their head and eyes, and to suppress eye blinks.

### **Auditory steady state response task description**

Auditory Steady State Response (ASSR) recordings will be performed. Subjects are seated in a comfortable chair and instructed to sit still, relax, and to close their eyes. They are also instructed to not pay special attention to auditory tones. Auditory stimuli are presented through headphones at a sound pressure level of 65 dB $\pm$  2 dB. Each stimulus is a 500ms burst of 1ms monophasic rectangular pulses at 40 Hz. The inter-stimulus interval is 700ms with no onset asynchrony.

### **Active auditory oddball task description**

Subjects are seated with EEG cap and headphones on and are instructed to sit still and relax. During the task, subjects are being presented auditory tones. Subjects are to pay attention to the tones and press a response-button when they hear an infrequent/deviant tone. A total of 500 tones are presented of which 400 are presented as frequent stimuli and 100 as deviant/infrequent stimuli. Therefore, infrequent tones have a probability of 0.2. The first five trials are frequent tones and there are at least two frequent tones between two deviant/infrequent tones. The frequent and infrequent tones are 150ms tones of 1000 Hz and 500 Hz at a sound pressure level of 75dB, respectively. All tones have a 5ms rise and fall time. Tones are presented at a fixed rate of 1 Hz.

### **Passive auditory oddball task description**

Subjects are seated with EEG cap and headphones on and are instructed to sit still and relax. During the task, subjects are watching a silent movie while being presented auditory tones. Subjects are not to pay special attention to the tones. A total of 750 tones are presented of which 600 are presented as frequent stimuli and 150 as deviant/infrequent stimuli. Therefore, infrequent tones have a probability of 0.2. The first five trials are frequent tones and there are at least two frequent tones between two deviant/infrequent tones. The frequent and infrequent tones are 150ms tones of 1000 Hz and 1200 Hz at a sound pressure level of 80dB, respectively. All tones have a 5ms rise and fall time. Tones are presented at a fixed rate of 2 Hz.

### **Visual evoked potentials task description**

Visual Evoked Potentials (VEPs) recordings will be performed. Subjects are seated in a comfortable chair while resting their head in a chin-rest mounted 58 cm from a screen. Subjects are instructed to sit still and watch a red cross on the screen. Visual stimuli are presented on a screen with a contrast higher than 80 [%] and a mean luminance of 50 [cd / m^2]. The stimuli are two types of checkerboard-patterns: 1.00 degrees width and 0.25 degrees width. There are a total of 320 phase reversals for each type of stimulus at a rate of 2 [Hz].

### **Intra-epidermal stimulation (IES)**

An electrode specifically designed for nociceptive stimulation [39] is placed on the volar forearm. The settings of the IES for two types of stimuli are given in **Table 3**:

**Table 3: Settings for IES**

|                                    | Type I | Type II |
|------------------------------------|---------------|----------------|
| Shape of pulse              | Square        | Square         |
| Pulse width (us)            | 210           | 210            |
| Number of pulses (#)        | 1             | 2              |
| Inter-pulse interval (ms)   | NA            | 10             |
| Inter-stimulus interval (s) | 2.5-3.5       | 2.5-3.5        |

The adaptive staircase procedure method by Doll et al. [40] will be used to estimate the detection thresholds and slopes of IES. Stimulating below twice the detection threshold will ensure preferential stimulation of A $\delta$  fibres (nociceptive system) [41].

Subjects are asked to release a push button when a stimulation is perceived. If the stimulation has not been perceived the adaptive staircase procedure will generate a new stimulus and the stimulation will be determined as not detected. The push button will also measure the reaction time between stimulation and release for IES.

Endpoints for both stimulus types:

- Detection thresholds (mA)
- Slope (mA-1)
- Rate of detection (%)
- Reaction time (ms)

These settings are in accordance with literature [41-44].

Baseline is defined as the value after a normal night of sleep.

### **Laser Stimulation (LS)**

LS will be performed by the STIMUL 1340 Nd:YAP laser system. The settings of the laser will be:

- Stimulus duration: 5 ms
- Laser diameter: 5 mm
- Energy: 2 J
- Energy density: 102 mJ/mm^2
- Inter-stimulus time: 6-8 s (randomized)
- For the LS assessments, only reaction time will be evaluated as psychophysical parameter during the tests. Subjects are asked to

Endpoint:

- Reaction time (ms)

The electrophysiological parameters will be the same as in the IES assessments. Due to the low signal to noise ratio (SNR) of EEG data, at least 15-40 stimulations are needed to find reliable LEP values [45, 46]. Therefore, in this study 20 stimulations will be used per location per stimulus block. EEG data will be collected with a cap using the 10-20 system. Artefacts due to eye blinking, etc. will be removed from the analysis.

The raw data will be analysed using FieldTrip by Matlab, giving the following:

Endpoints (in primary, secondary and control area):

- Amplitude ( $\mu$ V) of N1, N2, P1, P2, N2P2 peaks
- Latency (ms) of N1, N2, P1, P2, N2P2 peaks

These settings are in accordance with literature [45, 47, 48].

Baseline is defined as the value after a normal night of sleep.

### **PainCart assessments**

Nociceptive (pain) detection and tolerance thresholds will be measured using the PainCart, an integrated range of tests for measuring different modalities of nociception. The PainCart aims to assess as objectively as possible the levels of pain induced in human subjects by a variety of potentially noxious stimuli. All measurements will be performed in a quiet room with ambient illumination and temperature. During each testing session, there will only be 1 subject per room. During nociceptive tests, subjects will either be sitting or resting comfortably on a bed (high-Fowler's position, with knees supported).

Pain intensity will be measured continuously for each of the following nociceptive tests with subjects rating their pain intensity using a 100% electronic visual analog scale (eVAS)-slider, with 0 and 100

defined as 'no pain' and 'worst pain tolerable', respectively. The equipment is programmed to cease giving stimuli if pain intensity reaches the maximum possible score. Data from the eVAS will inform the PDT (the start of pain, when a subject moves the eVAS slider away from 0) and the PTT (when a subject moves the eVAS slider to the end point, triggering a stop for any particular pain test). In addition, the area under the VAS pain curve and/or post-test VAS may be determined for any of the pain tests performed in the study. The following tests will be performed:

### **Electrical Stimulation Pain Test (Electrical Stair and Burst)**

For cutaneous electrical pain, 2 electrodes (Ag-AgCl) will be placed on clean (scrubbed) skin overlying the left tibial bone 100 mm distal from the caudal end of the patella (middle of the first electrode is placed 100 mm distal the caudal end of the patella and middle of the second electrode 135 mm directly underneath the first). Electrical resistance between electrodes will be less than 2 k $\Omega$  [49].

For single (stair) stimulus, each stimulus (10-Hz tetanic pulse with a duration of 0.2 ms) will be controlled by a computer-controlled constant current stimulator. Current intensity will be increased from 0 mA in steps of 0.5 mA·s (cutoff 50 mA). The pain intensity after each stimulation will be measured using the eVAS, until pain tolerance level is reached or a maximum of 50 mA is reached. [49] To measure conditioned pain modulation (formerly diffuse noxious inhibitory control), the single stimulus will be repeated within 5 minutes of the end of the cold pressor task.

For repeated (burst) stimulus, each single stimulus is repeated 5 times with a frequency of 2 Hz. Pain threshold is taken as the value (mA) whereby a subject indicates either: all 5 stimuli are painful, or the train of 5 stimuli started feeling non-painful but ends feeling painful (VAS > 0) (Adapted from the method of Arendt-Nielsen et al, [50]).

### **Pressure Pain Test**

This method of pressure pain induction has been shown to primarily assess nociception generated from the muscle with minimal contribution by cutaneous nociceptors [51] and is based on methods previously described [52]. Briefly, an 11 cm wide tourniquet cuff (VBM Medizintechnik GmbH, Sulz, Germany) will be placed over the gastrocnemius muscle with a constant pressure rate increase of 0.5 kPa/s controlled by an electro-pneumatic regulator (ITV1030-31F2N3-Q, SMC Corporation, Tokyo, Japan), Power1401mkII analogue-to-digital converter and Spike2 software (CED, Cambridge, UK). The subject will sit comfortably with their foot flat on the floor and rate their pain intensity using the eVAS, with 0 and 100 defined as "no pain" and "worst pain tolerable", respectively. The pneumatic pressure will be increased until the subject indicates their PTT, or a maximum pressure of 100 kPa is achieved, at which point the device releases pressure to the tourniquet.

### **Cold Pressor Pain Test**

The method of cold pressor pain is based on the methods previously described [53, 54]. Subjects place their non-dominant hand into a water bath (minimal depth 200 mm) at 35  $\pm$  0.5 °C for 2 minutes. At 1 minute 45 seconds a blood pressure cuff on the upper-arm will be inflated to 20 mmHg below resting diastolic pressure. At 2 minutes the subject will then move their hand from the warm water bath, directly placing their hand into a similar sized bath at 1.0  $\pm$  0.5 °C. The subjects will be instructed to indicate when pain detection threshold is reached (first change in sensation from cold non-painful to painful) as well as the increase in pain intensity, by moving the eVAS slider. When pain tolerance is reached (sensation is no longer tolerable; eVAS slider at 100 mm), or when a time limit (120 s) is reached, subjects are instructed to remove their arm from the water, at which point the blood pressure cuff will deflate. Analysis of the recorded data results in the following parameters for cold pressor pain measurements are: Time from cold water immersion until pain detection threshold (seconds), pain tolerance threshold (seconds), and area above the curve (AC) (seconds\*mm).

### **Thermal Pain Tests**

To determine heat PDTs in normal skin as well as primary hyperalgesia to heat, thermal PDTs will be measured with a thermode (Medoc Q-Sense) with a contact area of 30 mm x 30 mm. The thermode

will be placed in the middle of the control or primary area on the subject's volar forearm, starting with the control. The initial temperature of the thermode will be 32°C and will increase by 0.5°C per second until the subject perceives the stimulus as painful, based on PDTs, or when a temperature of 50°C is reached. The average of a triplicate measurement will be used to determine PDTs.

### McGill Questionnaire

McGill's Pain Questionnaire (MPQ-DLV), [55-57] a classical pain questionnaire, which addresses the multiple dimensions of pain: sensory (temporal, spatial and descriptive), affective (autonomic and anxiety), evaluative and miscellaneous. The questionnaire consists of general pain questions (duration, location, radiation, and frequency), a pain word list (divided in twelve sensory, five affective, and three evaluative adjectives) and 10 cm visual analogue lines of pain intensity (current and minimum-maximum). The scoring algorithm sums the number and the rank orders of adjectives within each dimension, and measures the different visual analogue scores [55]. The McGill is particularly used to assess how patients perceive pain. The momentary 10-cm visual analogue lines alone, ranging from 0 ('no pain') to 100 mm ('worst pain conceivable') are well suited for repeated 'pharmacodynamic' pain measurements.

### Laboratory parameters

The following samples will be collected for the following clinical laboratory tests:

| Lab               | Tests                                                                        | Collection & Analysis                                                                                                             |
|-------------------|------------------------------------------------------------------------------|-----------------------------------------------------------------------------------------------------------------------------------|
| Alcohol           | Alcohol Breath Test                                                          | The hand-held Alco-Sensor IV meter (Honac, Apeldoorn, the Netherlands) will be used to measure the breath ethanol concentrations. |
| Urine drug screen | Cocaine, amphetamines, opiates (morphine), benzodiazepines and cannabinoids. | A urine specimen will be analysed at CHDR by test kit (InstAlert, Innovacon, San Diego, USA).                                     |

## 7.2 Safety and tolerability assessments

The definitions, reporting and follow-up of AEs, SAEs and potential pregnancies are described in section 8. There are no safety and tolerability assessments included in this study besides the investigator assessment during the driving test as well as the observation of adverse events.

### 7.2.1 Investigator assessment during driving test

#### Part A

There is a safety assessment in place to ensure the safety of the subjects. Before driving the subjects are instructed about the possibility to terminate the on-the-road driving test. The driving instructor will emphasize the possibility for early termination of the driving test. The test can also be prematurely stopped by the driving instructor when needed to ensure the safety of the subjects and other road-users.

## 8 SAFETY REPORTING

### 8.1 Definitions of adverse events

An Adverse Event (AE) is any untoward medical occurrence in a subject who is participating in a clinical study performed. The AE does not necessarily have to follow the administration of a study drug, or to have a causal relationship with the study drug. An AE can therefore be any unfavourable and unintended sign (including an abnormal laboratory or vital sign finding), symptom, or disease temporally associated with the study participation, whether or not it is related to the study drug.

#### 8.1.1 Intensity of adverse events

The intensity of clinical AEs is graded three-point scale as defined below:

- Mild: discomfort noticed but no disruption of normal daily activity;
- Moderate: discomfort sufficient to reduce or affect normal daily activity;
- Severe: inability to work or perform daily activity.

#### 8.1.2 Chronicity of adverse events

The chronicity of the AE will be classified by the investigator on a three-item scale as defined below:

- Single occasion: single event with limited duration;
- Intermittent: several episodes of an event, each of limited duration;
- Persistent: event which remained indefinitely.

#### 8.1.3 Action

Eventual actions taken will be recorded.

#### 8.1.4 Serious adverse events

A Serious Adverse Event (SAE) is defined by the International Conference on Harmonization (ICH) guidelines as any AE fulfilling at least one of the following criteria:

- results in death;
- is life threatening (at the time of the event);
- requires hospitalisation or prolongation of existing inpatients' hospitalisation;
- results in persistent or significant disability or incapacity;
- is a congenital anomaly or birth defect; or
- any other important medical event that did not result in any of the outcomes listed above due to medical or surgical intervention but could have been based upon appropriate judgement by the investigator.

An elective hospital admission will not be considered as a SAE.

#### 8.1.5 Reporting of serious adverse events

SAEs will be reported according to the following procedure.

The investigator will report the SAEs through the web portal ToetsingOnline (see <https://toetsingonline.nl/>) to the accredited EC that approved the protocol, within 7 days of first knowledge for SAEs that result in death or are life threatening followed by a period of maximum of 8 days to complete the initial preliminary report. All other SAEs will be reported within a period of maximum 15 days after the sponsor has first knowledge of the SAE.

**8.1.6 Follow-up of adverse events**

All AEs will be followed until they have abated or until a stable situation has been reached. Depending on the event, followup may require additional tests or medical procedures as indicated, and/or referral to the general physician or a medical specialist.

**8.2 Temporary halt for reasons of subject safety**

In accordance to section 10, subsection 4, of the WMO, the investigator will inform the subjects and the EC if anything occurs, on the basis of which it appears that the disadvantages of participation may be significantly greater than was foreseen in the research proposal. The study will be suspended pending further review by the EC, except insofar as suspension would jeopardise the subjects' health. The investigator will ensure that all subjects are kept informed.

## 9 STATISTICAL METHODOLOGY AND ANALYSES

### 9.1 Statistical analysis plan

All safety and statistical programming is conducted with SAS 9.4 for Windows or newer (SAS Institute Inc., Cary, NC, USA). A Statistical Analysis Plan (SAP) will be written and finalized before the study closure, i.e., database closure. The SAP will provide full details of the analyses, the data displays and the algorithms to be used for data derivations.

### 9.2 Protocol violations/deviations

Protocol deviations will be identified based on conditions related to the categories below:

- Protocol entry criteria
- Forbidden concomitant medications
- Missing evaluations for relevant endpoints
- Other protocol deviations occurring during study conduct.

Major protocol deviations will be identified before the study closure, and listed where appropriate.

### 9.3 Power calculation

#### Part A

For this power calculation we used aggregated data from a previous CHDR study (CHDR1429) in order to calculate the intra- and inter- SD. The variabilities are based on the change from SDLP values.

For a simulator driving test, a sample size of 24 will have a power of 0.80 to detect a difference in means of 3.88 cm, assuming a standard deviation of differences of 6.5 cm, using a paired t-test with a 0.05 two-sided significance level.

#### Part B

For this power calculation we used aggregated data from previous CHDR studies (CHDR1311, CHDR1422, CHDR1425, CHDR1431 and CHDR1440) in order to calculate the intra- and inter- SD. The variabilities are based on the change from baseline cold pressure pain test (coldPTT) values. For cold pressor pain test, a sample size of 24 will have a power of 0.80 to detect a difference in means of 2.09 (sec), assuming a standard deviation of differences of 3.5 (sec), using a paired t-test with a 0.050 two-sided significance level.

### 9.4 Missing, unused and spurious data

All missing or incomplete safety and pharmacodynamics (PD) data, including dates and times, are treated as such. Missing test results or assessments will not be imputed. Missing PD data, indicated as 'M' in the data listing, will be estimated within the statistical mixed model using SAS PROC MIXED.

#### Part A

Prematurely stopped on-the-road tests will only be included if more than 20 kilometres is driven, and only the last 10 kilometres will be used for data analysis.

The handling of missing, unused and spurious data will be documented in the study report.

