### 6.2 Pharmacodynamic endpoints

#### Part A

#### **Simulated and on the road driving**

- Standard deviation of lateral position (SDLP) (main parameter).
- Number of lane departures.
- Mean speed (MS).
- Standard deviation of speed (SDS).
- Perceived driving quality scale and perceived effort scale.
- Driving quality scale by driving instructor.
- Car driving exploratory biomarkers (drive safety score, head movements, steering wheel).

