### 7.1 Efficacy assessments

#### **On-the-road driving test**

Subjects will participate in validated on-road car driving tests. During these tests several safety precautions are taken to guarantee safety of the subjects and regular traffic. A licensed driving instructor (having access to dual controls) guards the safety of the subject and regular traffic during the test. In case the driving instructor or the subject is of the opinion that it is not safe to start or continue the driving test, the test will be interrupted. Subjects will operate a specially instrumented vehicle over a 55-km primary highway circuit, while maintaining a constant speed (95 km/h) and steady lateral position between the delineated boundaries of the right (slower) traffic lane. The subject will be allowed to deviate from this procedure only in order to overtake a slower vehicle traveling in the same traffic lane. The vehicle's speed and lateral position relative to the lane-lines is continuously recorded. These parameters are digitally sampled at 13 Hz by the MobilEye system (MobilEye Vision Technologies Ltd., Israel). Data is edited, off-line, to remove parts where data are disturbed by extraneous events (eg, passing maneuvers). SDLP (cm), ie, the weaving of the car, is the primary outcome variable. SDLP has been shown to be a sensitive measure to demonstrate dose-dependent differences from placebo for alcohol and psychoactive drugs including anxiolytics, antihistamines, antidepressants, hypnotics and analgesics, and drugs of abuse [4, 7, 25]. Standard Deviation of speed (SDS, km/h) will be a secondary variable. Mean lateral position (MLP, +/- cm), and mean speed (MS, km/h) are control variables. During screening, subjects will participate in a training driving test to become acquainted with the procedures of the driving test.

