### 9.8.1 Prematurely discontinued on-the-road driving tests

Before and during the on-the-road driving test the subject and/or the driving instructor can stop the test prematurely for safety reasons. This will be noted as an event and the events will be summarized.

The number of subjects who did not finish the test will be summarized by:

1. Person who stopped the test (subject or driving instructor);
2. Amount of kilometres driven (rounded to 5km);

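### Section 9.4 drops on-road drives stopped by 20 km and scores longer stopped drives on their last 10 km only, so the sleep-deprivation contrast depends on impairment-driven stops and unequal distances

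*Protocol*

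**What the plan says.** - **Rule for stopped drives (protocol, Section 9.4, Part A).** On-road drives stopped early "will only be included if more than 20 kilometres is driven, and only the last 10 kilometres will be used for data analysis". A drive stopped at or before 20 km is therefore lost.
- **Length of a completed drive (Section 7.1, on-the-road driving test).** Subjects drive "over a 55-km primary highway circuit". SDLP is named there as the primary outcome variable of this test.
- **Why drives stop (Section 9.8.1 on prematurely discontinued tests).** Before and during the drive, "the subject and/or the driving instructor can stop the test prematurely for safety reasons". Sections 7.1 and 7.2.1 say the same in substance. The planned summary is by who stopped the drive and by distance driven; sleep state is not listed.
- **Missing values (Section 9.4).** Nothing is imputed. Missing pharmacodynamic values "will be estimated within the statistical mixed model using SAS PROC MIXED". Section 9.9 gives that model a fixed group effect and a random subject effect.
- **Comparator (Section 3.1.2, Part A, and Section 9.9).** The comparator is the morning drive after normal sleep. No section trims it to a particular stretch.
- **Lane departures (Section 6.2).** The endpoint is "Number of lane departures", with no rate or distance adjustment stated.

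**The concern.** Whether a sleep-deprived drive enters the analysis, and over which kilometres, is decided by an event that the effect under study is likely to cause.

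- **Dropped drives.** The subject then has only a rested morning value in the primary analysis. That value says nothing about how far sleep deprivation worsened this person's driving. A mixed model that is valid under missing at random cannot restore the information.
- **Retained stopped drives.** Ten kilometres ending at the stop are set against a 55-km circuit. A drive stopped at 50 km loses 50 - 10 = 40 km of recorded data.

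At stake are the on-road SDLP and lane-departure contrasts, which serve the first Part A objective. The correlations of change in Section 9.9 are also affected, because they need a value in both states.

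**Working it through.** **1. The plan's own figure.** Sections 1.2.7 and 9.3 give N = 24, difference 3.88 cm, SD of differences 6.5 cm and two-sided alpha 0.05 for simulator SDLP. The noncentrality is 3.88/6.5 × √24 = 2.92 with 23 degrees of freedom. Exact paired-t power is 0.7997, so the stated 0.80 is reproduced. The stopped-drive rule does not apply to the simulator, so this figure is not in question. The protocol gives no figure for the rule itself.

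**2. Lane departures (arithmetic only).** Exposure ratio = 10/55 = 0.18.
- Apparent count ratio in a retained stopped drive = true rate ratio × 10/55. A true ratio of 3 gives 3 × 10/55 = 0.55, so worse driving looks like better driving.
- The count exceeds the rested count only if the rate per km is more than 55/10 = 5.5 times the rested rate.
- If 4 of 24 sleep-deprived drives are scored this way, a true group ratio of 3 appears as 3 × (20 + 4 × 10/55)/24 = 2.59.

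**3. Exclusion on its own.** The simulator's 3.88 and 6.5 cm are borrowed for scale only. In 40,000 simulated trials of 24 paired differences, the k most affected drives were removed, which is the extreme case:

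| Drives dropped | Expected contrast (cm) | Chance of significance |
|---|---|---|
| 0 | 3.88 | 0.80 |
| 1 | 3.33 | 0.71 |
| 2 | 2.86 | 0.60 |
| 4 | 2.02 | 0.40 |
| 6 | 1.23 | 0.23 |

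A softer version drops 15% of drives, with log-odds of dropping that rise with the subject's own SDLP increase. At 0.1 to 0.3 per cm the retained mean is 3.28 to 2.57 cm. At slope 0 it stays at 3.88 cm. The bias therefore comes from the dependence on impairment, not from the loss of drives as such.

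**4. Last 10 km against 55 km (assumed weaving models).**
- Slow drift in lane position, no worsening along the drive: 18.0-18.1 cm over the last 10 km against 19.0 cm over the full circuit.
- Weaving rising by 0.1 cm per km, stop at 54 km: 22.5 against 20.7 cm.
- The same rise, stop at 21 km: 19.2 against 20.7 cm.

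The mismatch can go either way.

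**5. Net effect on SDLP (illustrative).** Assumptions, none from the protocol: 11 segments of 5 km; rested level with mean 18 and SD 3 cm; day SD 1; segment noise SD 1.2; impairment with mean 4 and SD 4 cm, scaled from 0.6 to 1.4 along the drive; a stop when a 5-km segment exceeds a threshold; a threshold crossed only in the last segment counts as a completed drive. The estimate is the mean over retained pairs, and the true value is 4.00 cm.

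| Threshold (cm) | Deprived drives stopped | Of all drives, excluded | Estimate (cm) | Bias |
|---|---|---|---|---|
| 32 | 9% | 1.5% | 4.00 | nil |
| 30 | 16% | 4% | 3.87 | -3% |
| 28 | 26% | 10% | 3.59 | -10% |
| 26 | 38% | 20% | 3.14 | -22% |

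Bias = (estimate - 4.00)/4.00. In this model, drives stopped after 20 km are overstated by about 0.8 to 1.4 cm. That partly offsets the exclusion, and fully offsets it in the first row.

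**The case against.** The strongest reply is that this matters only if many drives are stopped, and the protocol gives no stop rate. That stands. With no stops there is no bias, and the illustrative model needs about a quarter of sleep-deprived drives stopped before the net SDLP bias reaches -10%. A reader might infer from the 38% row that the plan understates the on-road effect by about a fifth. The documents do not support that, because the on-road mean, its spread and the trigger for stopping are all assumed.

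A reader might also take the last 10 km to be the worst stretch. The protocol's criterion is a safety judgement by subject or instructor, not an SDLP level, and step 4 shows that the last 10 km can give the lower value.

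Nor does the rule undermine the sample size, which rests on the simulator. The study is exploratory, Section 1.2.6 counts all related parameters as main endpoints, and exclusion biases towards no effect, so it would not by itself produce a false positive SDLP result. Stops are also reported as events.

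Finally, Section 9.1 leaves derivation algorithms to the SAP, which is not at hand. The unmatched rested comparator and the unadjusted count are inferred from the protocol's silence, and an SAP could settle both. That does not dispose of the point: the 20-km exclusion and the last-10-km scoring are fixed in the protocol itself.

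**Conclusion.** The point holds in limited form. Followed as written, Section 9.4 makes inclusion of an on-road drive depend on impairment and measures retained stopped drives over a distance that is not comparable.

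- The direction of the exclusion effect is clear (towards no effect), provided that stops are related to impairment.
- The direction of the SDLP mismatch in retained stopped drives is not fixed.
- The lane-departure shortfall is certain for any retained stopped drive, unless the SAP converts the count to a rate.
- The net SDLP bias ranges from nil to -22% over the stop rates examined (9% to 38%), under the assumed model.

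The rule should be changed before the data are seen. It does not invalidate Part A. The same rule would also apply to a rested drive that was stopped.

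**What to change.** Replace the stopped-drive rule in Section 9.4 as follows.

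1. Keep all valid kilometres of every on-road drive, in both states.
2. Keep whole-drive SDLP as the reported outcome for completed drives. Estimate the state contrast with stopped drives included from a mixed model on equal-length segments, with state, distance and their interaction. State that segment SDLP is a different quantity from whole-drive SDLP, because it leaves out drift between segments.
3. Analyse lane departures per kilometre driven.
4. Add a sensitivity analysis that ranks a drive stopped or not started for safety as worst. Drives with little or no distance contribute little or nothing to the segment model, so this analysis is needed.
5. Tabulate stops by sleep state, beside the summaries already planned.

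The segment model is not a proven cure. It recovered the true contrast (4.22 against 4.25, 4.04 against 4.04 and 4.08 against 4.08 cm), but only with 1,500 simulated subjects and with stops triggered by the observed SDLP. Simply matching the distance of the two drives is not enough either: in the same kind of model it gave 3.32 to 3.86 against 4.00 cm.

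The cost is a rewording and some extra programming. Section 7.1 already has speed and lateral position recorded continuously, and Section 10.6.2 classes other statistical analyses as non-substantial amendments. The downside is noisier values for short drives.
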